# Spectacle wearing in children randomised to ready-made or custom spectacles, and potential cost savings to programmes: study protocol for a randomised controlled trial

**DOI:** 10.1186/s13063-016-1167-x

**Published:** 2016-01-19

**Keywords:** Uncorrected refractive errors, Children, School eye health, India, Spectacle wearing rate, Ready-made spectacles, Randomised clinical trial

## Abstract

**Background:**

Uncorrected refractive errors are the commonest cause of visual impairment in children, with myopia being the most frequent type. Myopia usually starts around 9 years of age and progresses throughout adolescence. Hyperopia usually affects younger children, and astigmatism affects all age groups. Many children have a combination of myopia and astigmatism. To correct refractive errors, the type and degree of refractive error are measured and appropriate corrective lenses prescribed and dispensed in the spectacle frame of choice. Custom spectacles (that is, with the correction specifically required for that individual) are required if astigmatism is present, and/or the refractive error differs between eyes. Spectacles without astigmatic correction and where the refractive error is the same in both eyes are straightforward to dispense. These are known as ’ready-made’ spectacles. High-quality spectacles of this type can be produced in high volume at an extremely low cost. Although spectacle correction improves visual function, a high proportion of children do not wear their spectacles for a variety of reasons. The aim of this study is to compare spectacle wear at 3–4 months amongst school children aged 11 to 15 years who have significant, simple uncorrected refractive error randomised to ready-made or custom spectacles of equivalent quality, and to evaluate cost savings to programmes. The study will take place in urban and semi-urban government schools in Bangalore, India. The hypothesis is that similar proportions of children randomised to ready-made or custom spectacles will be wearing their spectacles at 3–4 months.

**Methods/design:**

The trial is a randomised, non-inferiority, double masked clinical trial of children with simple uncorrected refractive errors. After screening, children will be randomised to ready-made or custom spectacles. Children will choose their preferred frame design. After 3–4 months the children will be followed up to assess spectacle wear.

**Discussion:**

Ready-made spectacles have benefits for providers as well as parents and children, as a wide range of prescriptions and frame types can be taken to schools and dispensed immediately. In contrast, custom spectacles have to be individually made up in optical laboratories, and taken back to the school and given to the correct child.

**Trial registration:**

ISRCTN14715120 (Controlled-Trials.com)

Date registered: 04 February 2015

## Background

Uncorrected refractive errors are the commonest cause of visual loss in children [1]. Myopia (short-sightedness) is the commonest form; it usually starts around the age of 9 to 10 years, progressing in severity throughout adolescence. Hypermetropia (long-sightedness), which is more common in younger children, usually resolves by around the age of 10 years. Astigmatism (distorted vision, measured in cylinders) affects all age groups and does not change over time. Myopia is far more common in Asian children, particularly in Southeast Asia. Many children with myopia also have some degree of astigmatism, and one of the standard ways of reporting refractive error is to use the ’spherical equivalent’, which is calculated as the sphere plus 0.5 x the cylinder, in dioptres (D). Refractive errors can also differ between eyes (anisometropia).

**Fig. 1 Fig1:**
[figure not shown]
Randomisation flow chart of activities. Flow chart shows a child’s journey and the activities involved from screening to deciding whether they are eligible for recruitment, then randomisation and follow-up

Correcting refractive errors requires the following steps: measuring visual acuity in each eye without any form of correction, followed by measurement of the type and degree of refractive errors in each eye, which can be done clinically (by retinoscopy) or by an automated refractometer. The next step is to use the findings to assess which corrective lenses give the best visual acuity in each eye, which are then prescribed. The next step is to dispense the spectacles, which entails ensuring that the optical centres of the lenses required align with the visual axis of each eye when mounted in the spectacle frames of choice. If an individual has astigmatism, the axis of the cylinder in the lens must align accurately with that of the eye. Custom spectacles are needed if astigmatism is present and/or the refractive error differs between eyes. Spectacles without astigmatic correction and where the refractive error is the same in both eyes (simple refractive error) are much more straightforward to dispense. Indeed, high-quality spectacles without astigmatic correction with a range of spherical powers (the same in each eye) are being mass produced at extremely low cost (0.5US$). Several different frame sizes are also available, allowing for variation in the distance between the visual axis in different age groups, gender and populations. These spectacles are called ’ready-made’ or ’off-the-shelf’ spectacles. From a programmatic perspective, prescribing ready-made spectacles has benefits for providers as well as parents and children, as a supply of ready-made spectacles with a wide range of prescriptions and frame types can be taken to the school and dispensed immediately. In contrast, custom spectacles have to be individually made up in optical laboratories, marked with the child’s name, and the spectacles taken back to the school and given to the correct child.

The prevalence of uncorrected refractive errors in children varies by country and by urban/rural location, for example, in India [2–4]. In one study in rural India, 4.1 % of children aged 7–15 years were myopic, and 61 % of visual impairment was due to uncorrected refractive errors [2]. In an urban Indian setting 7.4 % of children aged 5–15 years were myopic and 82 % of visual impairment was due to uncorrected refractive errors. In both studies older children had a higher prevalence of uncorrected refractive error than younger children [4]. Global estimates indicate that 13 million children have visual impairment due to uncorrected refractive errors [5]. A recent study in China provides evidence of what might be anticipated, that academic performance improves with correction of refractive error in children [6]. Studies have also highlighted that correcting refractive error is highly cost effective [7] and improves visual function and quality of life. These findings add impetus to the need for the inclusion of eye health into school health initiatives, which are being supported and scaled up by Ministries of Health and Education, the World Bank, WHO, UNESCO, UNICEF and the Partnership for Child Development. India has had a programme to detect and treat uncorrected refractive errors in school children since 1994 [8].

Approaches being used to detect and correct uncorrected refractive errors in children are not standardised, and spectacle wearing rates can be very low in all settings [5]. For example, in Native American students in the USA, only 32 % of children given two pairs of free spectacles wore their spectacles [9]. Similar findings have been reported from rural areas near Delhi where only 29.4 % of children wore their spectacles [10]. Spectacle wear is higher in children with more severe uncorrected refractive errors [9] and in girls [11]. In another study in India only 30 % of children dispensed spectacles were wearing them at 6–12 months. Spectacle wearing was higher amongst girls, those with higher refractive errors and poor uncorrected visual acuity, and those whose fathers were better educated [12].

Only four trials have assessed the impact of interventions to increase spectacle wear in children, three being in low/middle income countries. One compared spectacle wear at 3–6 months in school children in Tanzania who were randomised to free spectacles or a prescription. Spectacle wear was significantly higher amongst those given free spectacles (47 % versus 26 % respectively, *p* = 0.05) [13]. In a trial in China, children were randomised to attend or not attend a health education session. Children in the health education group actually had lower rates of spectacle wear at follow-up than the controls [14]. In another study in China, a health education DVD shown to parents, teachers and children increased self-reported wear but not observed wear [6].

One study has addressed the utility of ready-made spectacles in Chinese school children. In this study children with high degrees of astigmatism, anisometropia or eye disease (8 %) were excluded and the remainder were randomised to ready-made spectacles or custom spectacles regardless of the extent to which correction improved their visual acuity. The study was powered to detect at 15 % difference in spectacle wear, but at follow-up one month later spectacle wear was similar in both groups (47 % in the ready-made spectacles group and 52 % in the custom spectacles group (*p* = 0.23) [15].

Despite spectacle correction improving visual function [16], children do not wear their spectacles for a variety of reasons, such as no perceived benefit [17], loss or breakage [18–21], misconceptions that spectacles will make their vision worse [11, 13, 22], parental disapproval [10, 15], being teased [13, 15, 18, 21–23] and forgetfulness [14, 15, 19, 21]. In a recent Indian study [12], reasons for not wearing spectacles included being teased (19.8 %), the spectacles were broken (17.4 %) or lost (9.3 %), and the child did not like their spectacles (12 %). There is also evidence that the degree of visual impairment also influences spectacle wear. For example, in the Tanzanian trial outlined above, increasing myopia was an independent predictor of spectacle wear. In a recent study in Bangalore, designed to assess different visual acuity screening cut-offs, children wearing their spectacles at 3–4 months also had higher degrees of myopia than those who were not (mean spherical equivalent in the better seeing eye −3.50 D, range −1.75 to −9.00 D versus mean −2.50 D range −0.75 to −2.25 D respectively) (*p* = 0.001) (unpublished data).

### Purpose

The purpose of this trial is to compare spectacle wear at 3 to 4 months in school children aged 11 to 15 years with significant simple uncorrected refractive errors who are randomised to ready-made spectacles or custom spectacles, and to evaluate the potential cost savings to programmes.

The hypothesis is that similar proportions of children randomised to ready-made spectacles or custom spectacles will be wearing their spectacles at 3–4 months.

### Pilot study December 2014

A pilot study was undertaken in non-trial schools to test all aspects of the trial and to provide data for the sample size calculation, including the proportion of children with uncorrected refractive errors who would be eligible for ready-made spectacles.

## Methods/design

The trial is a randomised, non-inferiority, double masked clinical trial of children with simple uncorrected refractive errors. A non-inferiority design was chosen, as the benefits of ready-made spectacles are the considerably lower cost and ease of dispensing, both of which have the potential to increase the efficiency and cost effectiveness of programmes. As millions of children are affected by uncorrected refractive errors, the lower cost of ready-made spectacles also has the potential to increase coverage of school-based programmes. Under these circumstances a slightly lower acceptance of ready-made spectacles, measured by spectacle wearing, might be acceptable. The non-inferiority margin of 10 % was chosen to balance the considerations of efficacy and secondary benefits. The allocation ratio is approximately 1:1.

### Study setting

The trial is being undertaken in government middle and secondary schools in urban and peri-urban areas in and around Bangalore, Karnataka state, India. The trial is coordinated by Sankara Eye Hospital, Bangalore. The field team consists of optometrists, dispensing opticians, field workers and ophthalmologists, all of who are members of staff at the Sankara Eye Hospital. Training, quality assurance and oversight of data collection are being provided by staff at the International Centre for Eye Health, London School of Hygiene & Tropical Medicine.

### Participant eligibility

#### Inclusion criteria

For a student to be eligible for recruitment, he/she must be aged 11–15 years, be present at school at the time of screening, and meet all the following criteria: a) presenting visual acuity (with spectacles if usually worn) of less than 6/9 in both eyes, b) visual acuity with full correction improves in the better seeing eye by two or more lines, c) the spherical equivalent corrects the visual acuity to not more than one line less than best corrected visual acuity with a full prescription in the better eye, d) the difference between the spherical equivalent of the right and left eyes is not more than 1 D, e) the inter-pupillary distance (IPD) matches that of ready-made spectacle frames available (54 to 62 mm) and f) spectacle frames are of acceptable size and fit. Parents must consent for their child to take part in the study.

#### Exclusion criteria

The following children are not being recruited: those with other causes of visual loss or whose visual acuity does not improve by two lines or more with spherical equivalent lenses; there is more than 1 D of anisometropia or parents do not consent. All these children are being dispensed custom spectacles and are not recruited to the trial.

### Eligibility of those performing interventions

All refractions, prescribing and dispensing are being undertaken by fully qualified optometrists, including the lead investigator.

### Identification of potential participants and recruitment

In the schools selected for the trial, trained field workers measure visual acuity at the 6/9 level in each eye and with both eyes open, with spectacles if the child usually wears them. A LogMAR visual acuity chart in an illuminated cabinet is being used at the recommended test distance of 6 metres to overcome variable illumination in the classrooms. Children who pass the screening test are given a green card and sent to another field worker who registers their age and gender.

All children who fail screening undergo objective and subjective refraction by an optometrist. The following information is being recorded: objective refractive error and corrected visual acuity in each eye; subjective refractive error and best corrected visual acuity in each eye. The spherical equivalent is calculated for each eye, and visual acuities are measured and recorded for each eye using the spherical equivalent. An optometrist then decides whether the child is eligible for recruitment. All children requiring spectacles, whether eligible for the trial or not, are allowed to select the frames they prefer from a range of coloured plastic or metallic frames. The type of frame and the frame size needed are recorded.

All eligible children are given an information sheet and consent form for their parents to sign which they return to the school. A trained field worker goes through an assent form with each child. Each child is allocated a unique study number and randomised to ready-made spectacles or custom spectacles. All those recruited are given a red ID card that contains their name, their father’s name, a mobile telephone number and study ID. Children are asked to give the card to their class teacher so they can be identified when the trial spectacles are delivered a few weeks later, to ensure that each child receives the correct spectacles.

Children not eligible are either given a green card, if spectacles are not required, or a red card if they need custom spectacles or referral to Sankara Eye Hospital for assessment of other eye conditions. These findings are recorded by a field worker.

In both arms of the trial the same procedures are followed, including the day on which spectacles are delivered to the school. Before giving each child their spectacles, their identity is confirmed by a field worker using the red card issued at the time of recruitment. Corrected visual acuity with the new spectacles is also measured in each eye. Children not eligible for the trial who require custom spectacles also receive their spectacles at the same time.

Children, parents/carers, and teachers are not aware which type of spectacles (ready-made spectacles or custom spectacles) each child receives (Fig. 1).

### Sample size calculation

Parameters used in the sample size calculation include a significance level of 0.05, 95 % confidence interval, 90 % power and 1:1 allocation. The trial is powered to detect a non-inferiority margin (∆) of 10 %. No increase has been added for loss to follow-up, as all eligible children present on the day of the visit are being recruited, and high response rates are anticipated based on previous experience. Calculations, which were one sided, were performed using a web-based sample size calculation programme (Sealed Envelope, https://www.sealedenvelope.com/power/binary-noninferior/, accessed 31 October 2014). A sample of 240–260 eligible children will be required in each arm of the trial. The prevalence of uncorrected refractive errors in the earlier study in Bangalore was 4 %. Assuming approximately a third would not be eligible for ready-made spectacles, the effective prevalence would be 2.6 %; therefore, 20,000 children in 200 schools would need to be screened.

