#### Primary analysis

The proportion of children wearing or having their spectacles with them at school at 3 to 4 months will be compared between the intervention and comparator arms, using the risk difference with 95 % confidence intervals.

We will also calculate and present the risk ratio with 95 % confidence intervals.

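### The sample size is described as one-sided at 0.05 but the analysis uses 95% intervals, so the error rate of the non-inferiority decision is inconsistent as written; if the size was set at one-sided 5%, power is about 83%, not 90%

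*Protocol article*

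**What the plan says.** The Sample size calculation section of the protocol article lists its inputs in one sentence: "Parameters used in the sample size calculation include a significance level of 0.05, 95 % confidence interval, 90 % power and 1:1 allocation". The margin follows: "The trial is powered to detect a non-inferiority margin (∆) of 10" per cent. Two sentences later the direction is given: "Calculations, which were one sided, were performed using a web-based sample size calculation programme". The result is: "A sample of 240–260 eligible children will be required in each arm of the trial". Losses are not allowed for: "No increase has been added for loss to follow-up".

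Under Primary analysis, the proportions wearing spectacles "will be compared between the intervention and comparator arms, using the risk difference with 95" per cent confidence intervals. That section does not say whether the interval is one- or two-sided, or which limit is set against the margin.

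The wear proportion behind the sample size is not given. The Pilot study section says that the pilot was to supply data for the calculation, but reports no wear rate. Trial status gives 460 children recruited.

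**The concern.** Taken plainly, a one-sided calculation at significance level 0.05 spends 5% in the one direction that matters for non-inferiority. The interval that matches this test is a two-sided 90% interval. A two-sided 95% interval, which is what an unqualified 95% interval normally means, spends 2.5% in that direction. On the plain reading the trial was sized for one test and will be analysed with a stricter one.

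Two things are at stake. First, the stated 90% power may not belong to the planned analysis. Second, the verdict itself could turn on which sentence is followed. An observed deficit in the ready-made arm may clear the 10-point margin at one-sided 5% and fail at one-sided 2.5%. The section on cost savings makes the cost analysis conditional on non-inferiority being shown, so that verdict also decides whether the second aim is analysed.

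**Working it through.** **Inputs.** From the Sample size calculation section: power 90%, margin 0.10, 1:1 allocation, 240–260 per arm, no inflation for loss. From Trial status: 460 recruited, taken as 230 per arm. The even split is an assumption, since Methods/design says only that "The allocation ratio is approximately 1:1". The wear proportion p is not stated, so it is varied. Throughout, the true difference is taken as zero and the normal approximation with unpooled variance is used.

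**Step 1: trying to reproduce 240–260.**

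n per arm = (z₁₋α + z₀.₉₀)² × 2p(1−p) / 0.10²

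With z₀.₉₅ = 1.645, z₀.₉₇₅ = 1.960 and z₀.₉₀ = 1.282:

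| p | one-sided 5% | one-sided 2.5% |
|---|---|---|
| 0.30 | 360 | 442 |
| 0.50 | 429 | 526 |
| 0.80 | 275 | 337 |
| 0.82 | 253 | 311 |
| 0.83 | 242 | 297 |
| 0.86 | 207 | 254 |
| 0.87 | 194 | 238 |

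Solving for p, 240–260 per arm follows from wear of about 0.81–0.83 at one-sided 5%, or about 0.855–0.869 at one-sided 2.5%. The mirror values, 0.17–0.19 and 0.13–0.145, give the same sizes. The stated range can arise from either alpha, so it does not show which was used.

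**Step 2: power if the size was set at one-sided 5%.** A size that gives exactly 90% power at one-sided 5% makes margin/SE equal to 1.645 + 1.282. Power at one-sided 2.5% is then

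Φ(1.645 + 1.282 − 1.960) = Φ(0.967) ≈ 0.833.

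The wear rate cancels. To restore 90%, n must be multiplied by [(1.960 + 1.282)/(1.645 + 1.282)]² ≈ 1.227, which gives 295 to 320 per arm.

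**Step 3: power at actual recruitment.** Power = Φ(0.10/SE − z₁₋α), with SE = √(2p(1−p)/n). Under the one-sided 5% design take p = 0.82. At n = 230, SE = √(0.2952/230) = 0.0358 and 0.10/SE = 2.79.

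- One-sided 5%: Φ(2.79 − 1.645) ≈ 0.87.
- One-sided 2.5%: Φ(2.79 − 1.960) ≈ 0.80.

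Recruiting below target accounts for the fall from 90% to about 87%; the change of alpha accounts for the rest.

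**Step 4: power if the size was set at one-sided 2.5%.** With p = 0.86, power at one-sided 2.5% is 0.897 at 250 per arm, so the 90% stands at the planned size. At 230 per arm it is 0.871.

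**Step 5: where the verdict would differ.** The lower limit clears −10 points when the observed difference exceeds −10 + z × SE. With 230 per arm:

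- At 82% wear (SE 3.58 points): above −3.0 with a two-sided 95% interval, above −4.1 with a 90% interval.
- At 50% wear (SE 4.66 points): above −0.9 and −2.3 respectively.

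Deficits between each pair of values pass under one level and fail under the other.

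**The case against.** The strongest reply is that the documents are ambiguous rather than wrong. Two readings reconcile them.

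- The 95% interval is listed among the sample size inputs. The 0.05 could be the two-sided level, with the calculation one-sided only in direction, as any non-inferiority calculation is. Design and analysis would then both be one-sided 2.5%.
- The Primary analysis section does not call its interval two-sided. A one-sided 95% limit would match a one-sided 5% design.

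It can also be said that the exact decision rule is often left to the analysis plan, that a stricter analysis makes a false claim of non-inferiority less likely, and that recruitment has ended, so no restatement of power changes enrolment.

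Much of this stands. A reader might infer that the design and analysis statements cannot both be true and that the trial's power simply is 83%. The documents do not support that. The 82% wear rate is itself back-solved from the 5% assumption, and 2.5% with wear of about 86% gives the same size without loss.

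A reader might also take the wear rates quoted in the Background (about 30% in Indian studies, 47% and 52% in the earlier ready-made trial) and conclude that power is only 61–68% at 250 per arm under one-sided 2.5%. The article gives those rates as background and does not say that they entered the calculation.

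What the reply does not do is leave the text sound. On the first reading, 0.05 described as one-sided is the wrong label. On the second, nothing in the Primary analysis section signals a one-sided limit, and the risk ratio is given the same unqualified interval. This is a conflict in what the article states, not a detail deferred to another document.

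**Conclusion.** The point holds in a conditional form. As written, the one-sided error rate of the non-inferiority decision is either 5% or 2.5%, and the article supports both.

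- If 240–260 per arm was computed at one-sided 5% and the decision uses a conventional two-sided 95% interval, power is about 83% at the planned size, independent of the wear rate. At 460 recruited it is about 80%, assuming an even split and 82% wear.
- If it was computed at one-sided 2.5%, with wear near 86%, the 90% is right for the planned size and the description of alpha is wrong.

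The figures rest on a true difference of zero, the normal approximation and no loss to follow-up. The validity of the estimate and its interval is not affected. What is affected is the stated power and, for a small observed deficit, whether non-inferiority is declared.

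**What to change.** Before unblinding, state one rule: non-inferiority is concluded if the lower limit of the two-sided 95% confidence interval for ready-made minus custom is above −10 percentage points, which is a one-sided 2.5% test. In the sample size section, give the one-sided alpha and the wear proportion that were actually entered, and restate the power under that rule. If one-sided 5% was used, the figure is about 83% at the planned size. If one-sided 2.5% was used, keep the 90% and correct the description of alpha. The 83% should not be printed until the sponsor has confirmed which alpha was used.

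This takes a few sentences and no further children or data. The only cost is a possibly less favourable stated power.
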